**Methods:**

The HIGH-K Trial is a single-centre, double-blind, randomised controlled trial in adult, non-diabetic patients presenting to an Australian Emergency Department with hyperkalaemia (>5.5 mmol/L [99 mg/dL]). Ninety-five participants are randomised 1:1 to receive either glucose-only therapy (100 mL 50% dextrose bolus followed by 250 mL 10% dextrose infusion over 2 h) or standard IDT (10 units IV insulin with 25 g dextrose followed by 250 mL saline infusion). The primary safety outcome is the incidence of hypoglycaemia (<3.9 mmol/L [70 mg/dL]) within six hours. The primary non-inferiority outcome is the mean change in serum potassium from baseline to two hours, using a non-inferiority margin of −0.5 mmol/L (–9 mg/dL). Secondary outcomes include severity of hypoglycaemia, rescue insulin requirements, and serum insulin/C-peptide levels.

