**Figure 1. F0001:**
[figure not shown]
CONSORT diagram of participants in the HIGH K trial. HIGH K, Hypertonic glucose vs Insulin-dextrose to prevent HypoGlycaemia following treatment for hyperKalaemia; CONSORT Consolidated Standards of Reporting Trials; BGL, blood glucose level; IV, intravenous.

**Table 1. t0001:** Study inclusion and exclusion criteria.

Inclusion criteria	Exclusion criteria
1.Age >18 years.	1.History of diabetes mellitus or pre-treatment BGL >7.8 mmol/L (140 mg/dL).
2.Blood gas **or** serum potassium >5.5 mmol/L (99 mg/dL).	2.Requiring resuscitation (cardiac arrest, unstable arrhythmias, SBP <90mmHg, HR <45 BPM).
3.Treating clinician determines need for active treatment and agrees to enrol patient in the trial.	3.Intravenous insulin administered prior to randomisation.
4.Ability to provide informed consent or consent obtained by authorised substitute decision-maker.	4.Enrolled in the trial within the past 30 days or have previously been enrolled more than once.
	5.Suspected or confirmed intracranial/ intraspinal ischaemic or haemorrhagic stroke.
	6.Known glucose-galactose malabsorption syndrome.
	7.Known allergy to corn (maize) and corn products.

BGL: blood glucose level; SBP: systolic blood pressure; mmHg: millimetres of mercury; BPM: beats per minute.

Standard consent is provided in written form. However, if a patient is unable to provide a signature due to acute illness or the requirement for contact precautions (e.g. respiratory isolation), verbal consent will be obtained. In such instances, the verbal agreement must be witnessed and signed by two independent staff members to ensure procedural integrity. If a patient lacks decision-making capacity, written consent may be obtained from an authorised substitute decision-maker. Patients enrolled *via* a substitute decision-maker will be approached once capacity returns and offered the opportunity to either provide ongoing informed consent to continue in the study or withdraw their participation.

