### Intervention

Participants will be allocated *via* stratified (potassium <6.5 mmol/L [117 mg/dL] or ≥6.5 mmol/L [117 mg/dL), block randomisation to receive either glucose-only therapy or insulin–dextrose therapy (IDT) in a 1:1 ratio with the use of sequential, opaque, sealed envelopes. Envelopes are opened by members of the research team or clinical pharmacists only after formal participant enrolment is confirmed and documented. Interventions will be prepared by the same staff who open the envelope and away from clinical areas. Study solutions will appear visually identical to ensure blinding of participants and treating clinicians. The study period extends for six hours following randomisation. In eligible participants, treatment commences as soon as possible after enrolment.

In the glucose-only arm, participants will receive 100 mL of 50% dextrose administered over 10 min, followed immediately by 250 mL of 10% dextrose infused over two hours.

In the insulin–dextrose arm, participants will receive 10 units of intravenous insulin (Actrapid) mixed with 50 mL of 50% dextrose and 50 mL of 0.9% sodium chloride (total 100 mL), administered over 10 min, followed by 250 mL of 0.9% sodium chloride infused over two hours.

Infusion bag 1 (100 mL) will be prepared by modifying 0.9% sodium chloride bags according to the assigned intervention. Study labels will be affixed to the front of each bag. Infusion bag 2 (250 mL) will consist of the proprietary product used in each arm without alteration; these bags will be concealed using an opaque black sleeve to mask product identity, with study labels applied to the exterior.

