## Statistical considerations

The target sample size for this study is 95 enrolments (approximately 48 per treatment arm). This sample size was primarily determined to provide 80% power to detect a statistically significant difference in the incidence of hypoglycaemia, assuming an incidence of 17% in the IDT group and 0% in the glucose-only group, using a two-sided significance level (α) of 0.05.

To account for repeat enrolments (maximum of two per participant), a design effect of 1.1 was applied. This was derived from an assumed intra-class correlation coefficient (ICC) of 0.3 and an average of 1.2 enrolments per participant. The ICC was conservatively selected to reflect potential within-subject correlation in hypoglycaemia risk. The final figure of 95 enrolments includes a 10% buffer to account for attrition or missing data (e.g. missed blood glucose measurements or haemolysed potassium samples).

This sample size also provides sufficient power for the primary non-inferiority objective serum potassium reduction at two hours. With a non-inferiority margin of −0.5 mmol/L (–9 mg/dL), an assumed true mean difference of 0.0 mmol/L and a standard deviation of 0.8 mmol/L (14.4 mg/dL), a minimum of 82 enrolments is required to achieve 80% power (α = 0.025, one-sided). Thus, the planned recruitment of 95 enrolments ensures the study is adequately powered for both primary endpoints.

All analyses will adhere to a modified intention-to-treat (mITT) principle, including participants who are randomised, receive the assigned intervention, and have at least one post-baseline potassium and BGL measurement. For participants commencing dialysis within the 6-hour observation period, data up to the point of dialysis initiation will be included. Per-protocol analyses will be undertaken as sensitivity analyses to assess potential bias arising from treatment cross-over (patients in the glucose only group receiving insulin).

For the primary safety outcome (hypoglycaemia incidence), proportions will be summarised by treatment group, and the between-group difference will be reported with 95% confidence intervals (CI). Groups will be compared using Fisher’s exact test. If clustering due to repeat enrolments is evident, a generalised linear model with a binomial error structure and robust standard errors adjusted for clustering will be used.

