For the primary efficacy outcome (change in serum potassium at two hours), mean (SD) reductions in each group and the between-group mean difference (95% CI) will be reported. Non-inferiority will be concluded if the lower bound of the 95% CI is greater than −0.5 mmol/L (–9 mg/dL).

Secondary outcomes will be summarised descriptively by treatment group. To compare groups, general linear models will be calculated with an identity or binomial error structure for continuous or categorical outcomes. Group differences will be reported as mean differences (continuous) and risk differences or risk ratios (categorical) with 95% CIs. Repeated measures data will be analysed using linear mixed-effects models, which account for within-subject correlation and accommodate missing data.

Missing data will be managed based on the extent of data loss. If missingness is minimal (<5%), cases with missing data will be excluded from analysis. Potassium results from haemolysed samples will be counted as missing data. Mixed-effects modelling will allow the inclusion of all available data, mitigating bias related to incomplete measurements.

No adjustment for baseline covariates is planned, as randomisation is expected to achieve balance between treatment groups. A two-sided p-value of <0.05 will be considered statistically significant. All analyses will be performed using an appropriate statistical software package.

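### Repeat-enrolment correlation is provided for in the hypoglycaemia co-primary but not in the potassium non-inferiority interval or its sample size; the expected effect is small and the remedy is free

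*Protocol article*

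**What the plan says.** **Repeat enrolment is allowed.** Table 1, exclusion criterion 4, bars anyone "Enrolled in the trial within the past 30 days or have previously been enrolled more than once", so a second enrolment is possible after 30 days. Statistical considerations gives the same limit: "repeat enrolments (maximum of two per participant".

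**Allocation.** The Intervention section describes stratified block randomisation "in a 1:1 ratio with the use of sequential, opaque, sealed envelopes". It states no rule linking the arm at a second enrolment to the arm at the first.

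**Hypoglycaemia.** Statistical considerations states: "To account for repeat enrolments (maximum of two per participant), a design effect of 1.1 was applied". The factor comes from an ICC of 0.3 and an average of 1.2 enrolments per person, and the ICC is justified by within-person correlation in hypoglycaemia risk. In the analysis, a binomial model with cluster-robust standard errors replaces Fisher's exact test on a condition: "If clustering due to repeat enrolments is evident".

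**Potassium.** The same section gives a minimum of 82 enrolments (margin −0.5 mmol/L, true difference 0, SD 0.8, one-sided α 0.025, 80% power) and mentions no design effect for that figure. For the analysis, "mean (SD) reductions in each group and the between-group mean difference (95% CI) will be reported", and non-inferiority is declared if the lower limit lies above −0.5 mmol/L. Linear mixed models are named in the paragraph on secondary outcomes, for repeated measures, and again under missing data. Neither mention refers to repeat enrolments or to the primary interval.

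**Unit of counting.** The abstract says "Ninety-five participants are randomised 1:1 to receive either glucose-only therapy". Statistical considerations says "The target sample size for this study is 95 enrolments (approximately 48 per treatment arm".

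**The concern.** The two co-primary outcomes come from the same enrolments and the same people. The plan recognises within-person correlation for one outcome, in both sample size and analysis, and for the other in neither. The non-inferiority decision is read from one end of the potassium interval, so its standard error should reflect how the data arise. If a pair of enrolments falls in the same arm, positive correlation makes an unadjusted standard error too small; if the pair falls in opposite arms, it makes it too large. The plan controls neither case and names no method that would adapt to whichever occurs.

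The article also concludes that 95 enrolments give adequate power for both co-primary outcomes. For potassium, that conclusion rests on a figure computed without the inflation used for hypoglycaemia.

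**Working it through.** **Inputs.** From Statistical considerations: 95 enrolments, 1.2 enrolments per person, at most two each, ICC 0.3, design effect 1.1, loss 10%, SD 0.8, margin 0.5, true difference 0, one-sided α 0.025, power 80%. Two assumptions are added. The ICC of 0.3 is applied to potassium, for which the plan gives none. The arm at a second enrolment is taken as independent of the first, because no rule is stated.

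**1. The plan's 82.** n per arm = 2 × (1.960 + 0.842)² × 0.8² / 0.5² = 40.2, rounded up to 41, so 82 in total. This matches exactly, with no design effect.

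**2. People and pairs.** 95 / 1.2 = 79.2, so about 79 people; 95 − 79 = 16 of them are enrolled twice and 63 once.

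**3. The plan's 1.1.** The size-weighted form gives 1 + 0.3 × ((63 × 1 + 16 × 4)/95 − 1) = 1.101. The simple form gives 1 + (1.2 − 1) × 0.3 = 1.06.

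**4. Effect on the potassium standard error.** Unadjusted SE = 0.8 × √(4/95) = 0.164. With s same-arm pairs and o opposite-arm pairs (s + o = 16), the true variance is the unadjusted variance times 1 + 2 × 0.3 × (s − o)/95.

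| Split (same : opposite) | Variance factor | True SE | SE ratio | Coverage of unadjusted 95% CI |
|---|---|---|---|---|
| 16 : 0 | 1.101 | 0.172 | 1.049 | about 93.8% |
| 12 : 4 | 1.051 | 0.168 | 1.025 | about 94.4% |
| 8 : 8 | 1.000 | 0.164 | 1.000 | about 95% |
| 4 : 12 | 0.949 | 0.160 | 0.974 | about 95.6% |
| 0 : 16 | 0.899 | 0.156 | 0.948 | about 96.1% |

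The 16 : 0 row equals the size-weighted design effect in step 3, so the plan's 1.1 is the all-same-arm case.

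**5. How likely each split is.** If s is Binomial(16, 0.5), P(4 ≤ s ≤ 12) = 1 − 2 × 697/65,536 = 0.979. Each extreme has probability 2⁻¹⁶, about 0.000015. At 12 : 4 the 95% half-width moves from 0.322 to 0.322 × 1.025 = 0.330, less than 0.01 mmol/L.

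**6. Simulation check** (40,000 trials per setting, two-sample t interval). With independent allocation, coverage is 95.0% and one-sided error 2.5%. With all pairs in the same arm they are 93.8% and 3.1%; with all in opposite arms, 96.1% and 1.9%. At an ICC of 0.6 the two extremes give 92.6% and 97.1%, and independent allocation still gives 95.0%.

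**7. Sample size and power with the plan's own 1.1.** 82 × 1.1 = 90.2, so 91 evaluable, or 91/0.9 = about 101 enrolled. Normal-approximation power:

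| Evaluable enrolments | No design effect | Design effect 1.1 |
|---|---|---|
| 95 | 86.1% | 82.7% |
| 85.5 (95 less 10%) | 82.4% | 78.7% |

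**8. Waiting for clustering to be evident.** With 16 pairs and a true correlation of 0.3, Fisher's z is 0.31 × √13 = 1.12. A two-sided 5% test then has power Φ(1.12 − 1.96), about 20%, so such a condition would usually miss the correlation assumed here.

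**The case against.** **The method is simply not stated.** The article never says that enrolments are analysed as independent, it mentions mixed models in the same section, and the choice of standard error may sit in a fuller document. This stands in part: independence is inferred from the plain mean difference and the uninflated 82. But the article does specify the clustering method for the other co-primary, and its mixed-model sentences are not tied to this interval.

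**The effect is negligible on average.** This stands. A reader might infer that the potassium interval is too narrow and the non-inferiority test too liberal. The documents do not support that: with no rule for the second arm, an unadjusted interval is about nominal over the randomisation, and the 5% error belongs to splits that will in practice not occur.

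**The ICC is borrowed.** This also stands. The plan chose 0.3 for hypoglycaemia, and the true value for potassium may be lower or higher.

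**The 95 still suffices.** A reader might infer that the trial is underpowered for potassium. That goes too far: 91 is below 95, and power falls under 80% only when the full 10% loss is combined with the all-same-arm design effect. With independent allocation the expected inflation is near 1, and power at 85.5 evaluable is about 82%.

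**Conclusion.** The point holds as an inconsistency between the two co-primary outcomes and as a free improvement to the potassium analysis. It does not show a biased or invalid interval. With an ICC of 0.3 assumed for potassium, about 16 repeat pairs and independent allocation, average coverage is about 95%, and the standard error is typically within about 2.5% of the right value in either direction. The unfavourable planning case is 91 evaluable enrolments instead of 82, with about 79% power at about 85 evaluable.

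A participant-level term is still the better choice. It makes the interval fit whatever split occurs, and it gives a small gain in precision: with a known ICC, the generalised least squares SE is 0.161 against 0.165.

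The abstract's wording is a separate, minor correction. At the planned 1.2 enrolments per person, 95 overstates the number of people by 20% (95/79.2 = 1.2).

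**What to change.** - **Statistical considerations, primary efficacy outcome:** state that the between-group difference in potassium change and its 95% CI come from a linear model with a participant random intercept, or with participant-clustered standard errors. Use it unconditionally, not only when clustering is seen.
- **Statistical considerations, sample size:** state that the 82 assumes independent enrolments. Add that with the plan's own design effect of 1.1, the unfavourable case, it becomes 91 evaluable, and that power at about 85 evaluable is then about 79%.
- **Abstract, Methods:** replace participants with enrolments, to agree with Statistical considerations.

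The cost is one model term and two or three sentences. Limiting repeat enrolment already requires participant identity to be known, so no new data are needed, and the change calls for no extra recruitment. It should be fixed before the potassium data are analysed by arm.

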### Protocol amendments

Two formal amendments to the HREC-approved protocol have been implemented since trial commencement. Amendment 1 (approved 5/11/25) updated the patient consent procedure to permit verbal consent process discussed above.

Amendment 2 (approved 11/5/26) added serum C-peptide as a co-collected secondary/mechanistic endpoint at baseline, 1 h, and 2 h post-treatment, to provide a direct measure of endogenous insulin secretion and enable mechanistic characterisation of the glucose-only intervention. Participants enrolled prior to Amendment 2 will not have C-peptide samples collected; C-peptide analyses will therefore be restricted to eligible participants, and this will be acknowledged as a limitation in the final publication.

Protocol modifications are communicated to relevant parties *via* email and face-to-face follow up. The trial registration record (ACTRN12625000617460) has been updated accordingly.

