### Outcomes

The primary safety outcome is the incidence of hypoglycaemia (blood glucose <3.9 mmol/L (70 mg/dL), within 6 h post-treatment). Blood glucose is measured using validated bedside point-of-care glucometers. The primary non-inferiority outcome is the mean change in serum potassium (mmol/L) from baseline to 2 h post-treatment. Note that if a patient is enrolled based on a blood gas result due to clinical urgency, only the contemporaneous serum sample will be used for analysis. Secondary outcomes are severity of hypoglycaemia (ADA criteria); incidence of infusion-related complications including thrombophlebitis and extravasation; proportion of participants requiring rescue insulin therapy within 6 h post-treatment; mean change in serum potassium from baseline at 1 h and 4–6 h post-treatment; proportion of participants achieving a clinically significant potassium reduction (≥0.5 mmol/L [9 mg/dL] within 2 h); presence and resolution of hyperkalaemic ECG changes; serum insulin and C-peptide concentrations at baseline, 1 h, and 2 h post-treatment.

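### Insulin and C-peptide are measured at baseline, but the plan rules out adjusting for those values when the arms are compared at 1 h and 2 h

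*Protocol article*

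**What the plan says.** All quotes are from the Protocol article.

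- **Model and effect measure** (Statistical considerations). For secondary outcomes, "general linear models will be calculated with an identity or binomial error structure for continuous or categorical outcomes". The effect measure is then set: "Group differences will be reported as mean differences (continuous"), with 95% confidence intervals. No transformation is mentioned.
- **Repeated measurements** (same section). "Repeated measures data will be analysed using linear mixed-effects models". How baseline enters these models is not described.
- **Baseline** (same section). "No adjustment for baseline covariates is planned", on the ground that randomisation should make the arms alike.
- **The outcome** (Outcomes). The last secondary outcome is "serum insulin and C-peptide concentrations at baseline, 1 h, and 2 h post-treatment". Table 2 shows the same three sampling times.
- **The treatments** (Intervention). In the insulin–dextrose arm "participants will receive 10 units of intravenous insulin (Actrapid) mixed with 50 mL of 50% dextrose". The glucose-only arm receives no insulin.
- **Purpose and reach of C-peptide** (Protocol amendments). It was added "to provide a direct measure of endogenous insulin secretion and enable mechanistic characterisation of the glucose-only intervention". However, "Participants enrolled prior to Amendment 2 will not have C-peptide samples collected".

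The article gives no distribution, standard deviation, expected effect, baseline correlation or power for either analyte.

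**The concern.** Expected balance is a reason to think that an unadjusted comparison is unbiased. It is not a reason to forgo adjustment, whose main benefit in a randomised trial is a smaller standard error. Here the baseline samples are already scheduled, so using them needs no extra sampling.

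Precision matters most for C-peptide. It was introduced to show whether the glucose-only regimen raises endogenous insulin secretion, and it will be missing for everyone enrolled before the amendment. An analysis that leaves baseline out makes poorer use of an already reduced sample.

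The scale is a second, lesser matter. Concentrations are positive and often right-skewed, and injected insulin in one arm makes a large difference in serum insulin foreseeable. A difference in arithmetic means may then be an inefficient or poorly calibrated summary.

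**Working it through.** **1. Sample available.** The plan gives no figure for these outcomes; the cap is the target of 95 enrolments. That target reproduces from the stated inputs (17% v 0%, two-sided 0.05, 80% power) with an unpooled variance:

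- n per arm = (1.960 + 0.842)² × (0.17 × 0.83) / 0.17² = 38.3, so 39 per arm and 78 in total.
- 78 × 1.1 (design effect) = 85.8; × 1.1 (10% buffer) = 94.4, so 95.

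For C-peptide, assume even accrual from November 2025 to November 2027 and read the Amendment 2 approval date (11/5/26) as day/month. About 18 of 24 months remain: 95 × 18/24 = 71, or about 36 per arm before losses.

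**2. Gain from baseline adjustment.** With correlation ρ between baseline and follow-up, adjustment multiplies the standard error by √(1 − ρ²). A comparison that has 80% power unadjusted then has power Φ[(1.9600 + 0.8416)/√(1 − ρ²) − 1.9600]. The 80% is an illustration, not a claim of the protocol. Each ρ is an assumption, and repeat enrolments are ignored.

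| ρ | SE factor | Calculation | Power |
|---|---|---|---|
| 0.3 | √0.91 = 0.954 | Φ(2.937 − 1.960) = Φ(0.977) | 84% |
| 0.5 | √0.75 = 0.866 | Φ(3.235 − 1.960) = Φ(1.275) | 90% |
| 0.7 | √0.51 = 0.714 | Φ(3.923 − 1.960) = Φ(1.963) | 98% |

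For C-peptide, keeping 18/24 of the sample inflates the variance by 1/0.75. Adjustment at ρ = 0.5 multiplies it by 0.75. On these assumptions, adjustment would just offset the loss of enrolments before the amendment.

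**3. Does the planned mixed model already deliver this?** Only in some forms. Take complete data, equal variances and separate arm means at every time point. The between-arm contrast at 1 h or 2 h then has the unadjusted variance (factor 1). The contrast in change from baseline has factor 2(1 − ρ), which is 1.4, 1.0 and 0.6 at ρ = 0.3, 0.5 and 0.7. Constraining the arms to a common baseline mean gives about 1 − ρ², which is 0.91, 0.75 and 0.51. The article does not say which form is meant.

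**4. Scale.** This was checked by simulating 20,000 log-normal trials per scenario, with a single time point and no baseline. Log-SDs and ratios are assumptions. Coverage is that of the 95% interval for the untransformed mean difference (pooled t).

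| Scenario | Log-SD | Power, untransformed v log (48/arm) | Power, untransformed v log (36/arm) | Coverage (48; 36/arm) |
|---|---|---|---|---|
| 1.5-fold | 0.5 | 0.96 v 0.98 | 0.89 v 0.92 | 94.8%; 94.9% |
| 1.5-fold | 0.8 | 0.56 v 0.69 | 0.45 v 0.57 | 94.8%; 94.8% |
| 1.5-fold | 1.0 | 0.35 v 0.50 | 0.27 v 0.39 | 94.9%; 94.5% |
| 10-fold | 0.5 | both near 1 | both near 1 | 93.6%; 93.1% |
| 10-fold | 0.8 | both near 1 | both near 1 | 91.8%; 91.1% |
| 10-fold | 1.0 | both near 1 | both near 1 | 89.7%; 88.8% |
| 1.5-fold | 0.6 v 1.2 | 0.91 v 0.54 | 0.79 v 0.43 | 87.4%; 86.1% |

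With similar spread, power is lost at modest ratios, where coverage is sound. Coverage falls at large ratios, where power is not in question. With unequal spread the untransformed test rejects more often, because the two scales then estimate different things.

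**The case against.** The strongest reply is that the effect-measure sentence is a generic summary covering every continuous secondary outcome. These include potassium change, for which a mean difference is natural. The sentence does not name insulin or C-peptide and does not say that values stay untransformed. The choice of scale for an assay is commonly left to the analysis plan. This stands, and it is why the scale is only a preference here. An arithmetic difference in concentration is also a legitimate target, since the Introduction ties the potassium effect to the insulin level reached.

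The second reply is that three sampling times point to the mixed model, so the simulated single-time-point tests do not measure the loss under the planned analysis. This also stands for the scale figures. It does not dispose of the baseline point, because a mixed model gains this precision only if baseline is handled suitably, and the one explicit statement on baseline excludes adjustment.

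Three stronger readings are tempting and are not supported:

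- *The planned scale wastes power and gives poor intervals.* Both depend on spreads and ratios that the article does not give, and they arise mostly in different scenarios.
- *The arms will be tested against each other at baseline.* The Outcomes wording gives sampling times and announces no such test.
- *Injected insulin distorts both assays.* It bears on serum insulin. C-peptide was added as the direct measure of endogenous secretion, so the argument does not carry over. Nor would a log scale separate injected from endogenous insulin in the serum assay.

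**Conclusion.** The point holds for baseline adjustment. The plan excludes it for a reason that does not bear on precision, while the baseline values are collected anyway. The gain is about 4, 10 or 18 percentage points of power from a starting value of 80%, at assumed correlations of 0.3, 0.5 and 0.7. For serum insulin the correlation may be at the low end, because injected insulin could swamp the baseline level in one arm. That is an inference; the document gives no data on it.

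The log scale is a reasonable preference for positive, probably skewed measurements, and the article does not establish that a mean difference is wrong. The issue is one of precision in a secondary mechanistic analysis. It is minor and leaves the hypoglycaemia and two-hour potassium conclusions untouched.

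**What to change.** Add one or two sentences to the protocol or analysis plan before unblinded data are seen, for example: *Serum insulin and C-peptide at 1 h and 2 h will be compared between arms with the baseline value as covariate, or in the mixed-effects model with baseline means constrained to be equal between arms. Baseline values will be summarised by arm without comparison.* State that this is an exception to the rule of no baseline adjustment.

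Preferably specify log values (outcome and baseline) and report geometric mean ratios with 95% confidence intervals.

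No new samples or data are needed. Adjustment costs only the wording and a statement of how a missing baseline is handled. The log scale has a real cost: the estimand becomes a ratio of geometric means, and a rule for values below the assay limit must be fixed in advance. If the analysis plan already settles these points, it is enough to bring the protocol wording into line.

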**Figure 2. F0002:**
[figure not shown]
HIGH K study timeline; BGL, blood glucose level; ECG, Electrocardiography; IV, intravenous; PICF, patient information & consent form.

**Table 2. t0002:** HIGH K study assessments.

	Screening	Baseline	Hour 1	Hour 2	Hour 3	Hour 4	Hour 5	Hour 6	Post Discharge from ED
Eligibility	X	—	—	—	—	—	—	—	—
Screening	X	—	—	—	—	—	—	—	—
Randomisation	—	X	—	—	—	—	—	—	—
Demographics & baseline data	—	X	—	—	—	—	—	—	—
Comorbidities & medicines	—	X	—	—	—	—	—	—	—
BGL	—	X	X	X	X	X	X	X	—
Serum K^+^	—	X	X	X	—	—	X*	—	—
ECG	—	X	X	X	—	—	X*	—	X
Insulin level	—	X	X	X	—	—	—	—	—
C-peptide level^†^	—	X	X	X	—	—	—	—	—
Medications administered	—	—	—	—	—	—	—	—	X
Discharge destination	—	—	—	—	—	—	—	—	X
Protocol deviations	—	—	—	—	—	—	—	—	X
Adverse events	—	—	—	—	—	—	—	—	X

* Can be taken anytime within 4—6 h. ED = emergency department, BGL = blood glucose level, ECG = electrocardiograph.

^†^
C-peptide measurement was introduced as a protocol amendment shortly after trial commencement; data are available for all subsequent enrollments.

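### The 2 h potassium primary is stated as a raw mean difference that drops participants the mITT set keeps, and the plan's mixed model is not assigned to it

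*Protocol article*

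**What the plan says.** All points are from the protocol article.

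- **Endpoint (Outcomes).** "The primary non-inferiority outcome is the mean change in serum potassium (mmol/L) from baseline to 2 h post-treatment". Where enrolment rested on a blood gas, "only the contemporaneous serum sample will be used for analysis", so a gas value cannot stand in for an unusable baseline serum value.
- **Schedule (Table 2).** Serum potassium is taken at baseline, 1 h and 2 h, and once more later; the footnote to the later sample reads "Can be taken anytime within 4—6 h".
- **Analysis set (Statistical considerations).** Participants must be randomised, be treated and "have at least one post-baseline potassium and BGL measurement". Neither a usable baseline nor a 2 h potassium is required.
- **Dialysis (same section).** "For participants commencing dialysis within the 6-hour observation period, data up to the point of dialysis initiation will be included".
- **Primary estimate (same section).** "mean (SD) reductions in each group and the between-group mean difference (95% CI) will be reported", with non-inferiority judged by the lower 95% confidence limit against −0.5 mmol/L.
- **Missing data (same section).** "If missingness is minimal (<5%), cases with missing data will be excluded from analysis". Haemolysed potassium results count as missing. The paragraph closes by saying that mixed-effects models allow all available data to be used and so limit bias. The paragraph before it, on secondary outcomes, assigns linear mixed models to repeated-measures data.
- **Sample size (same section).** The 95 enrolments "includes a 10% buffer to account for attrition or missing data", with missed glucose readings and haemolysed potassium samples as examples.

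**The concern.** The analysis set and the primary estimate do not fit together. A participant with a valid 1 h potassium belongs to the mITT set, yet contributes nothing to a raw baseline-to-2 h difference if dialysis starts before 2 h, if the 2 h sample is missing or haemolysed, or if the baseline serum is haemolysed. The missing-data paragraph says handling depends on the extent of loss, but states a rule only for loss below 5%. It then mentions a mixed model without saying that this model governs the 2 h primary.

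Two different primary analyses could therefore be defended once the data are seen, and they can disagree on non-inferiority. The disagreement has a plausible direction. If glucose alone lowers potassium less, and a poor early fall leads to earlier dialysis, the raw difference loses more poor responders from the glucose-only arm. The observed difference then shrinks towards zero, which in a non-inferiority test is the anti-conservative direction. The 1 h value, which carries information about these participants, is already collected but goes unused.

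**Working it through.** **1. The plan's own figure.** Inputs from Statistical considerations: margin 0.5, SD 0.8, true difference 0, one-sided α 0.025, power 80%. Per arm n = 2(1.96 + 0.84)² × 0.8² / 0.5² = 40.2, rounded up to 41, or 82 in total. The stated 82 reproduces.

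**2. Power is not the main issue.** With 10% unscored, 95 × 0.9 = 85.5 enrolments remain. Power is 82.4% with no design effect, 80.1% with a design effect of 1.06 (1 + 0.2 × 0.3, from the plan's inputs) and 78.7% with the stated 1.1.

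**3. Reach of the exclusion rule.** 5% of 95 is 4.75, so the rule covers at most 4 enrolments. No rule is stated for 5 or more.

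**4. Bias in closed form.** Let a fraction q of one arm be unscored, with a mean reduction g lower than in the scored participants of that arm. The complete-case mean of that arm is too high by q × g. At a true difference of −0.5, false non-inferiority is 1 − Φ(1.96 − qg/SE). The values of q and g are assumptions; SD is 0.8, with 47.5 per arm before losses.

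Example: q = 10% in glucose-only, 0% in IDT, g = 0.8. The shift is 0.08. SE = 0.8 × √(1/42.75 + 1/47.5) = 0.169. 1.96 − 0.08/0.169 = 1.49, so the error is 6.9%.

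| Unscored (glucose-only / IDT) | g = 0.4 | g = 0.8 | g = 1.6 |
|---|---|---|---|
| 10% / 0% | 4.3% | 6.9% | 15.6% |
| 15% / 5% | 4.2% | 6.7% | 15.0% |
| 5% / 0% | 3.3% | 4.3% | 7.0% |
| 10% / 10%, same g | 2.5% | 2.5% | 2.5% |

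The third row lies inside the <5% rule overall, so small total loss does not by itself guarantee the nominal error.

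**5. Simulation with a response-driven mechanism.** Assumptions: 48 per arm, SD 0.8, 1 h–2 h correlation 0.7, IDT mean reduction 0.83 (the randomised trial cited in the Introduction), 10% of 2 h values lost overall, and response-driven loss confined to participants whose 1 h reduction is below a cut-off of 0, −0.2 or −0.4.

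To see what this implies by arm, take cut-off 0, a true difference of −0.5 and 1 h means equal to 2 h means. The share below the cut-off is Φ(−0.33/0.8) = 34% in glucose-only and Φ(−0.83/0.8) = 15% in IDT, averaging 24.5%. A loss probability of 0.10/0.245 = 0.41 among them gives about 14% against 6% unscored.

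Results at a true difference of −0.5:
- All loss response-driven: the raw difference averages −0.42 to −0.47. False non-inferiority is 3.8% to 7.6% over repeated runs, mostly about 4–7%.
- Half of the loss random: 3.2–4.4%.
- Three-quarters random: 2.7–3.2%.
- Likelihood estimate using the 1 h value, with all loss response-driven: 2.4–2.7%.

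At a true difference of −0.33 (0.5 against 0.83 in the cited trial), non-inferiority is declared in 21–30% of trials with the raw difference and 16–17% with the likelihood estimate. At a true difference of 0, the likelihood estimate costs about 2–5 points of power when loss is response-driven.

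**The case against.** The strongest reply is that the plan already deals with this. The sentence on mixed-effects modelling stands in the general missing-data paragraph, potassium is the only outcome that paragraph names, and potassium at baseline, 1 h and 2 h is itself repeated-measures data. One may read it as exclusion when loss is minimal and a mixed model otherwise. An analysis plan that is not shown may say so. This has weight: a reader might infer that these participants cannot be scored at all, and that is not so. They are lost to the raw difference, not to every analysis the document mentions. What stands is that the primary estimate is described as a raw difference, the mixed model is assigned only in the secondary-outcomes paragraph, and below 5% the text prescribes exclusion.

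A reader might also infer that a 5% rule contradicts a 10% budget. It does not. The 10% pools attrition, missed glucose readings and haemolysed potassium. It is a sample-size allowance, not a forecast of missing 2 h potassium.

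Third, the direction of bias is assumed. The article gives no rates of early dialysis, transfer or haemolysis by arm. It presents transfers as a logistical barrier, and nothing links haemolysis to arm or response. This also stands, and it limits the size of the claim.

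Last, the simulated mechanism depends only on the observed 1 h value, which favours the likelihood method by construction. If early dialysis follows something unrecorded, the model does not remove the bias.

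**Conclusion.** The concern holds as a mismatch within the article. The mITT definition, the endpoint, the dialysis rule and the stated primary estimate do not cover the same participants, and no method is named for those in the gap. That should be settled before unblinding.

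The consequence for error is conditional. Under the assumptions in the working, false non-inferiority is about 4–7% against 2.5% if all of a 10% loss is response-driven, about 3–4% if half is, and unchanged if loss is unrelated to response or equal in rate and kind in both arms. The documents do not support a claim that the primary will be biased, or that 10% of 2 h values will be missing. Confidence is medium: the mismatch is plain in the text, but its size depends on loss rates that the article does not give.

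**What to change.** In the primary efficacy paragraph of Statistical considerations:

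1. Make the primary potassium estimate the 2 h treatment contrast from one linear mixed model with serum potassium at baseline, 1 h and 2 h all as responses and a baseline mean common to both arms. Fit it to all mITT participants whatever the missing fraction, with participant-level clustering for repeat enrolments. Having baseline as a response keeps participants whose baseline sample was haemolysed.
2. Remove the <5% exclusion for this endpoint and keep the raw mean difference as a sensitivity analysis.
3. State that, for participants dialysed before 2 h, the model estimates the 2 h value without dialysis under missing-at-random.
4. Amend the sentence that rules out baseline covariate adjustment, because a common-baseline model in effect adjusts for baseline potassium.

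This is a wording change. The three samples are already in Table 2, and the sample size does not change. The costs are a slightly more complex primary analysis and about 2–5 points of power at a true difference of zero if loss is response-driven. The model corrects only for loss explained by observed potassium, not for loss that depends on unobserved response.
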